## Background

Atrial fibrillation (AF) is defined as a cardiac arrhythmia involving irregular atrial activation, uncoordinated atrial systole and ineffective ventricular filling. ECG shows no P wave but displays fast fibrillation waves different in form, size and rhythm that lead to an irregular ventricular response. Echocardiogram shows no mitral A wave valvular movement [1]. AF is the most frequent arrhythmia in clinical practice and a growing challenge to public health due to population aging. The estimated prevalence of AF is 0.4-1% in the general population and increases with age up to 5-6% in the population aged > 65 years, and 8% in subjects aged 80 years or older [2,3]. Similarly, while the incidence of AF is < 0.1% per year in subjects aged < 40 years, it increases to above 1.5% per year in women and 2% in men aged > 80 years [4]. The incidence of AF was expected to increase 5-fold by the year 2010 [5-8]. According to the Framingham Heart Study, lifetime risk for AF is 1 in 4 in men and women aged 40 years or older. Lifetime risks remain greater even in absence of congestive heart failure or myocardial infarction (1 in 6) [9]. AF is one of the fastest-growing cardiovascular epidemics of the 21^st^ century, as it is one the major causes of morbidity and mortality, and it increases death risk, congestive heart failure and the risk for embolisms –including strokes [6,10-12]. One in every six strokes occur in subjects with AF [13,14], and the increased risk for ictus depends on the number of additional risk factors. In addition, the quality of life of these patients is severely impaired, mainly due to their inability to perform daily activities as a result of the risk of exacerbation of symptoms [15]. Over the last 20 years, admissions for AF have increased by 66% as a result of population aging, the increasing prevalence of chronic heart diseases, the more frequent diagnosis by ambulatory control mechanisms, and other factors [16].

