**-Sociodemographic:**		
Age	≥ 65 years	Quantitative Discrete
Sex	Man/woman	Dichotomous Qualitative
Marital Status	bachelor, married, widow/er, divorced	Qualitative Polytomous
Residence	Urban (≥ 10.000 population)/Rural (<10.000 population)	Dichotomous Qualitative

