### -Statistical Analysis

Statistical analysis will be performed with the statistics analysis software EPIDAT 3.1 [29], SPSS [33], and WLwiN 2.02 [34]. It will include:

a. Descriptive Analysis: characteristics of the population under study (sociodemographic variables): central tendency, dispersion and position measures for quantitative variables; and tabulation and calculation of relative frequencies for qualitative variables. A calculation of major estimators with their corresponding 95% confidence intervals (CI95%) will be performed.

b. Bivariate Analysis: We will examine basal comparability between the two groups using the chi-square test or Fisher’s test (proportion comparison test), or by Student’s t-test (mean comparison test after testing normal distribution). Then, the AF dependent variable will be examined and crossed with the sociodemographic variables and other independent or prognostic variables of interest. On such purpose, we will use Pearson’s chi square tests or Fisher’s test (qualitative variables), and Student’s t-test or ANOVA (quantitative variables). All contrasts will be bilateral (p < 0.05).

c. Analysis of the relationship between the type of intervention and the primary variable of the study (AF): contingency tables, square chi test, relative risk estimation), attributable risk and number of subjects to be treated, with their respective CI95%.

d. Multivariate Analysis: A multi-level logistic regression or multiple logistic regression will be performed to compare effects of the strategy on both groups (Odds Ratio) adjusting the model for potential prognostic and / or confounding candidate variables. When multiple logistic regression is used, these variables will be introduced by the “Enter” technique. Significance will be > 0.10 according to Wald’s test.

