### Protection against bias

The study is open, so the intervention cannot be masked. Therefore, both, patients and practitioners will know who is involved in the intervention, and this might condition their response (Hawthorne effect), especially in the control group. Just the fact that the participants are identified and express their wish to participate in the study, and since they are subject to more intensive monitoring than usual, might make them more willing to follow medical advice.

Information bias can occur through errors in FA identification on the ECG due the practitioner’s inadequate skills. Practitioners will previously take a training course. The degree of interobserver reliability and agreement on blood pulse measuring will be examined.

Another bias might occur in the selection of patients, as one of the groups might include more patients diagnosed with AF before the study period. Should this occur in the control group, the beneficial effect of screening might be overestimated. Randomization will help balance both groups.

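### Attributable risk and NNT are planned only from a crude table, and age and sex are not fixed in the adjusted model, although randomising practitioners does not secure equal patient age between arms

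*Protocol article*

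**What the plan says.** **Effect measures.** In the Statistical Analysis section of the protocol article, item c covers the intervention against the primary variable. It lists "contingency tables, square chi test, relative risk estimation), attributable risk and number of subjects to be treated, with their respective CI95" and names no covariate.

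**Adjusted analysis.** Item d states: "A multi-level logistic regression or multiple logistic regression will be performed to compare effects of the strategy on both groups (Odds Ratio". The covariate set is left open: the article speaks only of "adjusting the model for potential prognostic and / or confounding candidate variables" and names none. It adds "Significance will be > 0.10 according to Wald’s test" without saying what that threshold decides. The article does not say whether c or d is primary.

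**Baseline check.** Item b says "We will examine basal comparability between the two groups" and gives no consequence for item c.

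**Age and sex.** Table 1 records both for each patient, age as "Quantitative Discrete". The Background says AF prevalence "increases with age up to 5-6% in the population aged > 65 years, and 8% in subjects aged 80 years or older".

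**How patients enter.** The Randomisation section assigns practitioners, stratified by centre and profession. The Sample size section says patients are then sampled consecutively. The Interventions section has the experimental group (EG) screen everyone seen, while the control group (CG) takes patients with listed symptoms or sequels. The Protection against bias section says the study is open. The Design section also uses the term individual randomisation, but the Abstract, Sample size and Randomisation sections all allocate practitioners, and that reading is used here.

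**The concern.** Randomising practitioners balances practitioners. Patients enter after the allocation is known and by a different rule in each arm, so their age distribution can differ systematically. Neither stratification factor is a patient characteristic. If one arm is older, it has more undiagnosed AF to find, and a crude table attributes that to the strategy.

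An older control group pulls the crude RR and risk difference towards no effect; a younger one inflates them. A systematic imbalance of this kind does not shrink as more patients are recruited.

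The absolute measures matter most here, because the Discussion hopes that the result will enter clinical practice guidelines. They are also the measures for which no adjusted version is planned.

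**Working it through.** **1. The plan's own figures.** The Sample size section gives risks of 1.63% (EG) and 1.012% (CG).
- RR = 1.63/1.012 = 1.61 (the article prints 1.62).
- Risk difference = 1.63 - 1.012 = 0.618 points; NNT = 100/0.618 = 162.
- Odds ratio = (0.0163/0.9837)/(0.01012/0.98988) = 1.62.
- The 10% inflation reproduces exactly: 7 722/0.9 = 8 580 and 3 861/0.9 = 4 290.
- The base size of 7 722 is within 3% of several standard two-proportion formulas (for example, 7 847 with an unweighted pooled proportion). The size-weighted pooled formula gives about 8 270. With that formula, 7 722 v 3 861 has 77% power at a two-sided 5% level, before clustering.

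The odds ratio and RR differ by only 0.01, so the adjusted odds ratio in item d can stand in for an adjusted RR. It does not give an adjusted risk difference or NNT.

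**2. Assumptions not in the documents.** (i) 25% of EG patients are aged 80 or older. (ii) Undiagnosed AF follows the same age gradient as the prevalence in the Background. (iii) The CG has 35% aged 80 or older.

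**3. Age gradient.** With overall prevalence P over age 65 and 8% at 80 or older, prevalence at 65-79 is (P - 0.25 × 8)/0.75. The old-to-young ratio r is 8 divided by that.

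| P | AF at 65-79 | r |
|---|---|---|
| 6% | 5.33% | 1.50 |
| 5.5% | 4.67% | 1.71 |
| 5% | 4.00% | 2.00 |

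**4. Effect on the crude measures.** Factor f = [1 + (r - 1) × 0.25]/[1 + (r - 1) × 0.35]. The crude RR is 1.611 × f, the CG risk becomes 1.012/f, and NNT = 100/(1.63 - CG risk).

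| r | f | Crude RR | CG risk | NNT | Power, 7 722 v 3 861 |
|---|---|---|---|---|---|
| 1.50 | 1.125/1.175 = 0.957 | 1.54 | 1.057% | 175 | 70% |
| 1.71 | 1.179/1.250 = 0.943 | 1.52 | 1.073% | 180 | 67% |
| 2.00 | 1.250/1.350 = 0.926 | 1.49 | 1.093% | 186 | 63% |

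**5. Other imbalances.** If the CG is 10 points younger (15% aged 80 or older), f is 1.125/1.075 = 1.047 to 1.250/1.150 = 1.087. The crude RR becomes 1.69-1.75 and the NNT 151-143. With the CG 5 to 15 points older and P from 6% to 5%, f runs from 0.98 to 0.89.

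**6. Against sampling error.** Expected AF cases are 7 722 × 1.63% = 126 and 3 861 × 1.012% = 39, together 165. The standard error of log RR is √(0.9837/125.9 + 0.9899/39.1) = 0.182. The 95% CI around 1.61 is therefore about 1.13 to 2.30, ignoring clustering. The shifts above lie well inside it.

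**The case against.** **Adjustment is already planned.** A reader might infer from item c that any age difference passes straight into the trial's only effect estimate. The documents do not support that. Item d plans a covariate-adjusted comparison of the same two strategies, the Abstract names multilevel logistic regression, and the adjusted odds ratio is nearly an adjusted RR. This objection stands and limits the point to the absolute measures and the unfixed covariates.

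**Covariate lists are often left to other documents.** Table 1 lists age and sex as independent variables, item b crosses AF with the sociodemographic variables, and the Enter method in item d is not stepwise. This also stands: not naming age and sex is, on its own, detail that an article may omit. The choice of a crude table for attributable risk and NNT is different, because the article states it.

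**Randomisation and imbalance.** The sentence "Randomization will help balance both groups" might be read as the plan's reason for not adjusting for age. It is not: that paragraph concerns patients diagnosed with AF before the study.

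**Ten points is a large imbalance.** Consecutive sampling limits practitioners' choice of patients, and with 269 practitioners chance alone is unlikely to produce a difference that large. It would have to come from systematic selection. The different entry rules make that possible, but nothing in the article gives its size or direction.

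**The larger difference lies elsewhere.** The CG takes patients with symptoms or sequels and the EG takes everyone. Age-sex adjustment does not make those populations comparable, and an adjusted NNT must not be presented as if it did. This stands and belongs in the fix.

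**Conclusion.** The point holds in a limited form. Attributable risk and NNT are specified only as crude measures, in a design where randomisation does not secure equal patient age and where age and sex are already recorded. The RR is largely covered by item d, provided that age and sex are in that model, which the plan does not guarantee.

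On the stated assumptions, a control group 10 points older moves the crude RR from 1.61 to 1.49-1.54 and the NNT from 162 to 175-186. A younger one moves them the opposite way. The 25% share, the 10-point difference and the transfer of the prevalence gradient to undiagnosed AF are all assumed. The shift is modest and smaller than the sampling error, and it would be wrong to call the age gradient steep within this age range on the Background's figures. The change is worth making because it costs little, not because the crude analysis is shown to mislead.

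**What to change.** - **Item d:** keep age (continuous) and sex as fixed covariates in the multilevel model, whatever their Wald p-values.
- **Item c:** report RR, risk difference and number needed to screen standardised from that model to the age-sex distribution of the whole sample, with confidence intervals that account for practitioners. Keep the crude table as descriptive.
- **Limit to state:** this removes only the age-sex part of any imbalance, and not the difference made by the symptom-based control-group entry rule.

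The cost is about two sentences of text and a little more analysis work. No new data are needed, and about 165 expected AF cases are enough for two fixed covariates.

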### Protection against bias

The study is open, so the intervention cannot be masked. Therefore, both, patients and practitioners will know who is involved in the intervention, and this might condition their response (Hawthorne effect), especially in the control group. Just the fact that the participants are identified and express their wish to participate in the study, and since they are subject to more intensive monitoring than usual, might make them more willing to follow medical advice.

Information bias can occur through errors in FA identification on the ECG due the practitioner’s inadequate skills. Practitioners will previously take a training course. The degree of interobserver reliability and agreement on blood pulse measuring will be examined.

Another bias might occur in the selection of patients, as one of the groups might include more patients diagnosed with AF before the study period. Should this occur in the control group, the beneficial effect of screening might be overestimated. Randomization will help balance both groups.

## Discussión

### Impact of results

This study will assess the effectiveness of early detection of AF. If our hypothesis is confirmed, we expect Primary Care professionals to take a more proactive approach and adopt a new protocol when a patient meeting the established screening criteria is identified. Finally, we expect this measure to be incorporated into Clinical Practice Guidelines.

### Ethical considerations

The research project has been approved by the Ethics Committees of the Hospital de Mataró (Barcelona) and the Hospital Reina Sofía (Córdoba). Informed consent will be previously obtained from all participants. This project will be conducted under the provisions of the Declaration of Helsinki, the European Council agreement on Human Rights and Biomedicine, and the UNESCO Universal Declaration.

The design and development of this study will be performed within Best Practice and Confidentiality norms (protection of personal data) and other national and international laws in force regulating health research.

This trial is registered in ClinicalTrials.gob (NCT01291953).

### Organization and logistics of the study

Systematic tracking of the fieldwork will be performed by a technical instructor, a monthly phone conversation with every practitioner, and collecting recruitment and DCF data. Subsequently, a case-based reasoning will be submitted to each practitioner.

Coordination meetings with the project management team will be held via Second Life (http://secondlife.com/) at least once every two months over the study period.
